### Ethical considerations and declarations

The study will be based on data collected for a study that was granted ethical approval on November 15, 2021 by the Swedish Ethical Review Authority (Dnr 2021–04552), addendums for the ethics approval were approved on May 20, 2022 (Dnr 2022-02454-02) and November 23, 2022 (Dnr 2022-05932-02). Informed consent will be obtained from all individual participants included in the study. The current study will be performed in line with the principles of the Declaration of Helsinki and its later amendments, as well as GDPR ethical rules. Ethical approval will be sought for any substantive changes to the protocol.

### The status and timeline of the study

Data collection has begun in Fall 2022 and is ongoing.

## Discussion

This study will offer understanding of how interventions can promote children’s mental health when delivered at different developmental stages. Findings will increase our understanding of the extent to which a SEL program delivered by teachers in preschool may have long lasting effects on adolescents’ mental health. Further, results will provide knowledge regarding the possible booster effects of an online parenting program (PW) on adolescents’ mental health. Considering the high numbers of children and adolescents with mental health problems and disorders [46, 47], especially during COVID-19 [48] it is of value to assess the usefulness of tools for mental health promotion as well as for prevention of problems during childhood and adolescence. Although universal, the intervention may be useful for parents and adolescents in need of further support and could reduce the use of mental health care resources. The universal aspect of the program could encourage positive family interactions, reducing conflicts in this stage of adolescent independence. If the study implies significant gains, the intervention could easily be offered to parents in general which is beneficial regarding scale-up [49].

The present project promises several new insights and innovations that are noteworthy. Scientific contributions within the area of social emotional learning (SEL) pertain to the six- to eight-year follow up of the PATHS intervention, which will be conducted in this project (i.e., pre-test data). PATHS is a SEL intervention that aims to directly support the development of emotion regulation, a key aspect of social emotional competence. Long term follow ups are rare, especially outside of the U.S., and only two prior studies have followed-up preschool SEL intervention for more than four years. In this project, the long-term impact of an intervention to support preschool children’s social emotional competence will be documented. Furthermore, the project advances our knowledge about developmental trajectories relevant to emotion regulation and mental health, which can inform wider SEL interventions.

Regarding the booster intervention, study of the effects of the Parent Web (PW) contributes to the field of evidence-based parent training interventions, which are generally associated with improved mental health and well-being in children and parents. In previous research, the selected version of the PW intervention showed promising effects, with reductions in parent reported externalizing behavior in youth as well as reduced depressive symptoms and stress in parents [30]. The present trial will investigate whether PW is effective at the universal level. This will lay the groundwork for more evidence-based options for universal parent training with the goal of enhancing mental health and well-being for families with adolescents. Since the PW connects with parents online, it provides an easily accessible parent training program, thus representing an ideal type of intervention. This is especially important considering the COVID-19 pandemic and the subsequent increased demand for greater flexibility via digital services, which may be vital to addressing health inequalities.

Because this is a booster intervention for a particular cohort of families who had prior participation in the preschool edition of PATHS, the generalizability of study findings is not as robust as it would be if this was a one-time new study enrollment with a wider pool of families. Other limitations to the current design are that this is a quasi- rather than randomized controlled trial. Advantages to this study design and trial are that the effects of multiple universal interventions with families are tested, and this trial is tested in an effectiveness trial approach with also gives insight into study recruitment and intervention completion expectations for future intervention trials of PW.

We expect to report project findings in open access scientific publications (e.g., peer reviewed). We also plan to create annual project updates distributed through our project website and to engage in outreach about our study and the topics that are involved in the project (via meetings, a project forum event with community stakeholders). Study results will not be described until all relevant project activities are completed. All results are reported at a group level.

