## Abstract

Well implemented, universal parental support is often effective in families with younger children, but research on their effects on families with adolescent children is scarce. In this study, a trial of the universal parent training intervention “Parent Web” in early adolescence is added to the social emotional learning intervention Promoting Alternative Thinking Strategies (PATHS®), completed in early childhood. The Parent Web is a universal online parenting intervention based on social learning theory. The intervention aims to promote positive parenting and family interaction through five weekly modules completed over 6–8 weeks. The main hypothesis is that participants in the intervention group will exhibit significant pre- to post- intervention-related benefits relative participants in the comparison group. The aims of this study are: 1) provide Parent Web as a booster aimed at improving parenting support and practices at the transition into adolescence to a cohort of parents whose children have previously participated in preschool PATHS, and 2) examine the effects of the universal edition of Parent Web. The study has a quasi-experimental design with pre- and post-testing. The incremental effects of this internet-delivered parent training intervention are tested in parents of early adolescents (11–13 years) who participated in PATHS when 4–5 years old compared to a matched sample of adolescents with no prior experience of PATHS. The primary outcomes are parent reported child behavior and family relationships. Secondary outcomes include self-reported parent health and stress. The proposed study is one of the few trials to test the effects of universal parental support in families of early adolescents and will therefore contribute to the understanding of how mental health in children and young people can be promoted across developmental periods through a continuum of universal measures.

**Trial registration:** Clinical trials.gov (NCT05172297), prospectively registered on December 29, 2021.

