## Materials and methods

### Aim, design, and setting

The proposed study aims to develop our understanding of how mental health in children and young people can be promoted across developmental periods through a continuum of universal measures. This study will be carried out as a non-randomized controlled experiment (i.e., quasi-experiment) with a matched wait-list control condition and with dependent pre- and post-tests [29]. The study examines the incremental effects of an internet-delivered parent training for parents of early adolescents (11–13 years old) who participated in a preschool implemented social-emotional learning (SEL) intervention (PATHS) when 4–5 years old (i.e., intervention group) compared to a matched sample (i.e., comparison group).The main hypothesis is that participants in the intervention group will exhibit significant pre- to posttest intervention related benefits relative participants in the comparison group on several key outcomes.

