### Matching procedure

The recruitment pool of families will be identified via Statistics Sweden’s national registry. Matching will be made on the following variables: PATHS child’s gender, age (birthdates within 6 months), and living in the same postal code and/or municipality as the primary residence of the matched PATHS child. Statistics Sweden will identify a matched recruitment pool of families and provide contact information for the matched families to the research team (parents’ and matched child’s name, phone number, matched child’s home address). The research team is responsible for recruitment of all study participants.

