### Data analysis plan

The main hypothesis that participants in the Parent Web condition will exhibit intervention-related pre- to posttest benefits relative to participants in the comparison group will be evaluated using two-wave two-group latent curve models [42] for each of the outcome variables. The pretest level of each outcome will be modeled as a latent intercept, and pre- to posttest change in the outcome will be modeled as a latent slope. Group 1 will be the intervention group comprised of participants in Parent Web. Group 2 will be the matched wait-list control comparison group.

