#### Model estimation and model testing

All models will be estimated in Mplus 8.4 [43] using a robust maximum likelihood estimator and a Huber-White adjustment to the standard errors and chi square test of model fit, as implemented in Mplus’s TYPE = COMPLEX feature, to consider cluster sampling of participants within schools. Each model will be assessed with the chi square test of exact fit and its *p*-value, the comparative fit index (CFI), the Tucker-Lewis index (TLI), the root mean square error of approximation (RMSEA), and the standardized root mean square residual (SRMR). Good model fit will be indicated by: chi square *p*-value > .05, CFI > .95, TLI > .95, RMSEA < .06, and SRMR < .08 [44].

The main hypothesis will be evaluated for each outcome variable by comparing Models A-D using the Bayesian information criterion (BIC). When comparing models, lower BIC indicates better relative model fit; a BIC difference of greater than 10 indicates very strong evidence against the model with the largest BIC [45]. If Model D is selected, then the difference in change between the groups will be evaluated by constraining the mean and variance of the latent slope to be equal across groups and comparing this model with an unconstrained model using the Satorra-Bentler nested chi-square test for robust maximum likelihood. In addition, the sensitivity of each selected model to the assumption of pretest equivalence between groups will be tested by constraining the mean and variance of the latent intercept to be equal across groups and comparing this model with an unconstrained model, as suggested by [42].

To assess power for this analysis, we conducted a Monte Carlo simulation using Model D. The model included two groups (intervention and comparison), latent intercepts and slopes for both groups, and three continuous indicators (e.g., parcels) at both pretest and posttest. We specified population values of .70 for all standardized factor loadings and a mean difference of .50 between the latent slopes of the two groups. We assumed a sample size of 288, with 144 in each group. Under these assumptions and using 1,000 replications and a robust maximum likelihood estimator, the power estimate for the group difference in latent slopes was .88.

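### The pre-test contrast with a matched, non-randomised sample cannot document the long-term impact of preschool PATHS and should be described as an observational comparison

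*Protocol article*

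**What the plan says.** The Discussion of the protocol article counts among the project's contributions a "six- to eight-year follow up of the PATHS intervention, which will be conducted in this project (i.e., pre-test data"), and then states that "the long-term impact of an intervention to support preschool children’s social emotional competence will be documented". The second sentence carries no qualification.

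The design is described under Aim, design, and setting as a "non-randomized controlled experiment (i.e., quasi-experiment) with a matched wait-list control condition". According to the Abstract, the PATHS cohort is "compared to a matched sample of adolescents with no prior experience of PATHS". The Matching procedure lists the matching variables as "PATHS child’s gender, age (birthdates within 6 months), and living in the same postal code and/or municipality". Under Target population and sample size, the PATHS side is limited to families whose child was in the earlier trial and whose parents had agreed to be contacted again.

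In the Data analysis plan, "The pretest level of each outcome will be modeled as a latent intercept". Under Model estimation and model testing, "the sensitivity of each selected model to the assumption of pretest equivalence between groups will be tested", by equating the intercept mean and variance across groups and comparing the result with a model without that constraint.

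**The concern.** The word impact is causal. To support it, the T1 comparison would need a comparator that differs from the PATHS cohort only in exposure to PATHS, or at least adequate control of the other differences. The design described was built for a different purpose, the change from pre- to post-test under Parent Web. At T1 the two groups differ in PATHS history, in how they came to be in the study, and possibly in family circumstances that the matching does not cover.

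If the sentence stands, a T1 difference produced by selection or by social background could be published as a lasting effect of a preschool programme. Conversely, an imprecise null could be taken to show that PATHS had no lasting effect, or that the groups are comparable.

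**Working it through.** **1. Which contrast is available at T1.** The Discussion names no comparator for the PATHS follow-up. The study recruits two groups: parents of the PATHS cohort and parents of the registry-matched sample. The matched sample as comparator is therefore an inference, but it is the only between-group T1 contrast that the article describes. The Swedish PATHS project section reports a cluster-randomised trial with 140 children in the PATHS arm and 145 in the wait-list arm, and the wait-list arm is not named as comparator. Whether those children later received PATHS is not stated. If they did, a randomised long-term contrast may no longer exist, but that would not make the matched contrast causal.

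**2. What a T1 difference contains.** Write

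T1 difference = P + S + U,

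where P is any lasting PATHS effect, S is selection (earlier trial participation and consent to future contact on one side only), and U is family differences left after matching on gender, age and area. One observed quantity cannot separate three unknowns. A larger sample narrows the interval around the sum and leaves the split unknown. Household income, education, home language, and parent age and gender are recorded at T1 but are not matching variables. Adjusting for them can reduce U. It cannot remove S, and because they are measured years after PATHS it does not recreate a baseline.

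A side point: the target population is given as 144 children, against 140 in the original PATHS arm, and inclusion asks only that the child took part in the trial. These passages should be reconciled, since they define who counts as exposed. The conclusion does not depend on it.

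**3. What the intercept-equality check can show.** It tests whether the sum P + S + U is zero. A non-significant result does not show P = 0, because components can offset each other, and it does not show that the groups are equivalent unless the interval is narrow.

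**4. The plan's own power figure.** The stated 0.88 is for a slope difference of 0.50 with 144 per group, three indicators and loadings of 0.70.
- Composite reliability = (3 × 0.70)² / [(3 × 0.70)² + 3 × (1 − 0.49)] = 4.41 / 5.94 = 0.742.
- Error variance in the factor metric = 1/0.742 − 1 = 0.347 per wave.
- The slope variance, the intercept–slope covariance and alpha are not given. Assuming two-sided 0.05 and a normal approximation, total variance 1 + 2 × 0.347 = 1.694 gives power 0.903, 1.894 gives 0.869, and 2.041 gives 0.844.

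So 0.88 is attainable under plausible unstated inputs and is not shown to be wrong. It concerns the slope difference only and says nothing about the T1 contrast.

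**5. Precision of the T1 contrast.** Assumptions: 144 per group with complete data, latent SD 1, error variance 0.347, two-sided 0.05, no clustering.
- SE = √(1.347 × 2/144) = 0.137.
- 95% half-width = 1.96 × 0.137 = 0.27 SD.
- Difference detectable with 80% power = 2.80 × 0.137 = 0.38 SD.
- Power for differences of 0.1, 0.2, 0.3 and 0.4 SD: 0.11, 0.31, 0.59 and 0.83.

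A true difference of 0.2 SD would be missed about 69% of the time. These figures bear on how to read a null result. They do not measure the confounding in step 2.

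**The case against.** The strongest reply is that this is one sentence in a Discussion. The PATHS follow-up is not among the stated aims or in the main hypothesis. The same section also asks, more cautiously, how far preschool learning may have lasting effects. The quasi-experimental design is listed as a limitation. The detailed follow-up analysis, with covariates, may sit in a fuller plan that is not shown. Much of this stands: the point concerns a claim, not the primary analysis, and the absence of an adjusted T1 analysis from a journal article is not in itself a fault. However, the limitation is stated in general terms and not tied to the PATHS claim, and no unseen plan could make the matched contrast randomised.

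A reader might go further and infer a contradiction: the Discussion would treat the T1 difference as PATHS impact while the analysis relies on "the assumption of pretest equivalence between groups". The text does not support this. Nothing under Data analysis plan or Model specification equates the intercepts across groups. Equality is imposed only in a sensitivity comparison against an unconstrained model, so a lasting PATHS difference would show up there without breaking the main slope comparison. Nor does the article say that a null T1 result will be reported as comparability or as absence of a PATHS effect. That is a risk to guard against, not a stated plan.

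**Conclusion.** The point holds as one about the conclusion drawn from the T1 data. The unqualified statement that long-term PATHS impact will be documented claims more than a non-randomised contrast can support when it is matched on gender, age and area and selected on one side. It rests on one inference, that the matched sample is the intended comparator, because no other is recruited.

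The documents give no basis for putting a number on the bias. What can be sized is the weakness of a null: about ±0.27 latent SD, and power of about 0.31 for 0.2 SD, under the assumptions listed in the working. Non-response would widen the interval, and clustering ordinarily would too. The main hypothesis, the slope models and the stated power of 0.88 are unaffected.

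**What to change.** 1. Reword the Discussion so that the T1 comparison is an observational comparison of PATHS-cohort families with matched families without PATHS, and drop the promise to document long-term impact.
2. Report that comparison as an estimate with a 95% CI, adjusted for background variables already collected at T1 (household income, parental education, home language, parent age and gender), and say that selection into the PATHS cohort remains uncontrolled.
3. Under Model estimation and model testing, state that the intercept-equality check is only a sensitivity check for the slope comparison, and that a non-significant result shows neither equivalence of the groups nor absence of a PATHS effect.

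The main slope models stay as they are. No new data are needed. The cost is some rewording, one extra adjusted analysis and a weaker claim about PATHS.
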